**Methods:**

This trial is a prospective, pilot phase-IIa, parallel-group RCT with three arms (two add-on treatment groups [BLT, EI] and one treatment as usual [TAU] control group). The primary outcome variable is change in the Inventory of Depressive Symptomatology total score (observer-blinded assessment) between baseline and ten weeks of intervention. This variable is analyzed with a mixed model for repeated measures approach investigating the treatment effect with respect to all three groups. A total of 330 participants with ADHD, aged 14 – < 30 years, will be screened at the four study centers. To establish effect sizes, the sample size was planned at the liberal significance level of α = 0.10 (two-sided) and the power of 1-β = 80% in order to find medium effects. Secondary outcomes measures including change in obesity, ADHD symptoms, general psychopathology, health-related quality of life, neurocognitive function, chronotype, and physical fitness are explored after the end of the intervention and at the 12-week follow-up.

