### Participant timeline

The trial time flow is shown in Figs. 2 and 3. At T1, the diagnosis of ADHD is established by performing structured clinical interviews. The Kiddie-Schedule for Affective Disorders and Schizophrenia - Present and Lifetime Version (K-SADS-PL) [85] is used to assess ADHD symptoms and co-morbid conditions in adolescents. To obtain as much information as possible for high valid diagnoses, both with regard to externalizing and internalizing conditions, the K-SADS-PL will be conducted separately with the adolescent and at least one primary caregiver. For the final rating, the trained clinician will take both sources of information into account. In adults, the Diagnostic Interview for ADHD in adults (DIVA) [86] is administered to assess ADHD symptoms and the Structured Clinical Interview for DSM-IV Axis I and II Disorders (SCID-I and II) [87] to assess co-morbid conditions. The Adult ADHD Self-Report Scale (ASRS) [88] and the Wender-Reimherr Adult ADHD Symptom Rating Scale (WRAADDS) [89] are used to substantiate diagnosis. All interviews and questionnaires will be adjusted to DSM-5 criteria. After having established the diagnosis of ADHD and having completed screening for eligibility based on interviews/questionnaires (Alcohol Use Identification Test [AUDIT] [90], National Institute on Drug Abuse [NIDA] Quick Screen [91], Physical Activity Readiness Questionnaire [PAR-Q] [92], physical examination, and IQ tests [Wechsler Adult Intelligence Scale, WAIS-IV [93]/ Wechsler Intelligence Scale for Children, WISC-IV [94]], informed consent is obtained. Trial-specific assessments are done at T1 after informed consent has been obtained and m-health will be introduced to participants and their parents (if applicable) (T1, duration = approximately 5 h for adults and 3.5 h for children/parents including breaks). Within two weeks after T1, the one-week baseline assessment with the m-Health system takes place at home. During this week, participants will wear the light and movement sensors on two working days and on Saturday and Sunday (always 24 h) and they will be asked to answer questionnaires (regarding mood regulation, reward and stress reactivity, sleep behavior, inattention, and context) 12 times a day (duration = 1 min each) provided by the m-health app. A subset of adult participants from Frankfurt are also asked to collect saliva on one day of the one-week period at home ten times over 24 h (immediately after awakening: approximately at 07:00, 30 min after wakening: approximately at 7:30 am, 11.00 am, 6.00 pm, 7.00 pm, 8.00 pm, 9.00 pm, 10.00 pm, midnight, 1.00 am) by chewing on a cotton swab which will be stored in tubes (Salivette™, Sarstedt, Germany). All participants are asked to fill out several questionnaires on the last day of the one-week period (duration = approximately 1 h) and to bring them along at T2. Baseline assessment based on interviews, questionnaires, body parameters/ fitness tests, and neurocognitive tests will be finished at T2 (duration = approximately 4 h for adults and children/parents including breaks) which is scheduled within three weeks after T1 and within one working week after the one-week m-health baseline assessment. Thus, all primary and secondary outcome measures are obtained either at T1, T2, or during the one-week baseline assessment. The randomization takes place at T2. Participants will be instructed in how to use the m-health app for the respective therapy and they will be introduced to all devices. Experimental groups will begin with the interventions the next day, while the control group continues with TAU which lasts for ten weeks. One week after T2, participants will be contacted via email to administer the Rey Auditory Verbal Learning Test (RAVLT) [95] recognition subtest (by sending a link via email to an online survey, 10 min). T3 (mid-intervention assessment) will take place five weeks after T2 (± 3 days). This mid-intervention assessment aims at obtaining the primary and secondary outcome measures during the ongoing trial to get some information on participants dropping out from the study before T4 (duration of T3 = approximately 3 h for adults and children/parents including breaks). Experimental groups will continue with the interventions for another five weeks while the control group continues with TAU. After ten weeks of intervention or TAU (control group) (five weeks after T3 ± 3 days), primary and secondary outcome measures are assessed again (duration = approximately 4 h for adults and children/parents including breaks), followed by a one-week post-intervention assessment with the m-health system including the same parameters as during the baseline m-health assessment. Saliva will be taken during one day of the one-week period (using the same procedure as during the baseline assessment) in the Frankfurt subgroup. One week after T4, participants will be contacted via email to administer the RAVLT recognition subtest. To assess the stability of the therapy effects, the study also includes a follow-up (T5) assessment 12–14 weeks after T4 (T5, duration = approximately 4 h for adults and children/parents including breaks). One week after T5, participants will be contacted via email to administer the RAVLT recognition subtest.

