### Statistical methods

#### Primary outcome

Statistical methods are used to assess the quality of data, the homogeneity of the treatment groups, the efficacy endpoints, and the safety of the three treatment groups. The confirmatory analysis of the primary endpoint will be conducted on the basis of the ITT population. An additional analysis will be conducted for the per-protocol (PP) population that includes all participants without major protocol violations.

A closed testing procedure will be applied controlling the overall type I error rate at 0.05 (two-sided). A mixed model for repeated measures (MMRM) approach investigating the treatment effect with respect to all three intervention groups will be used. Two-group comparisons I-1 vs TAU, I-2 vs TAU, and I-1 vs I-2 based on contrasts will follow. Baseline IDS-C_30_, age, IQ, sex, treatment, and center will be included as covariates. The MMRM approach models jointly all actual observations without imputing missing data but using the within-participant correlation structure to provide information about unobserved post-baseline primary endpoints. Gender effects are of particular interest. If there are not enough events per category for the different covariates, gender effects will be excluded from the MMRM analysis and investigated in a secondary analysis. The MMRM approach, by which the missing values with respect to post-baseline primary outcomes are dealt with, demonstrates favorable characteristics in terms of type I error rate, power, and bias of estimates compared to alternative methods dealing with missing values, such as last-observation-carried-forward (LOCF) [98–100].

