#### Additional analyses

Descriptive methods will be used for the analysis of the secondary outcomes, including the calculation of appropriate summary measures of the empirical distribution (mean, standard deviation, median, minimum and maximum for continuous variables, and frequency in percentages for categorical variables) as well as calculation of descriptive two-sided *p* values. A special focus of the exploratory analysis will be with respect to the time course of the primary as well as the secondary endpoints. Additionally, sensitivity analyses will be conducted for different populations (PP population, appropriate subgroups) and applying different imputation techniques (such as LOCF) for missing values. Further exploratory analyses will be performed to identify intervention effects in subgroups and potential prognostic factors (including hormone levels) for an intervention effect. Furthermore, variables possibly mediating treatment effects such as reward processing, stress reactivity, and compliance with the interventions will be explored. Appropriate regression will be used following the four-step procedure by Baron and Kenny [101]. Graphical methods will be applied to visualize the findings of the study. The safety analysis will be based on the set of all randomized participants who were exposed to study intervention at least once and includes calculation and comparison of frequencies and rates of adverse and serious adverse events reported in the two intervention groups. All analyses will be done using SAS version 9.4 or higher. A statistical analysis plan will be written before the final analysis.

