### Monitoring

The study will be monitored by the KKS Heidelberg, a university-based institution which is independent from other trial staff and very experienced in monitoring clinical trials. Monitoring will be done by on-site and off-site visits and frequent communication (letters, telephone, facsimile, email) by a clinical monitor according to SOPs of the KKS and the study-specific monitoring manual. The monitor will ensure that the trial is conducted according to the protocol and regulatory requirements by review of source documents, entries into the CRFs, and essential documents. The monitor will document the visits in a report for the PI as well as the local primary investigator. The site will be provided with a follow-up letter of the findings and the necessary actions to be taken. As the monitoring strategy will consider current aspects of risk-based quality management, frequency of monitoring activities per site will vary depending on recruitment, experience, and general performance, e.g. quality of documentation of the individual trial sites. If there are major findings during monitoring or an audit, the investigational site might be closed by the trial coordinator/PI.

In addition to the standardized monitoring procedures, an independent DSMB has been established that supervises the conduct of the trial and issues recommendations for early termination, modifications, or continuation of the trial, if necessary. The DSMB involves two independent clinical experts and one biometrician for monitoring the progress of the trial and ensure adherence to protocol. The role of the DSMB will be to monitor the progress of the trial and to ensure adherence to protocol. The character of the interventions under investigation makes unexpected SAEs extremely unlikely. For pragmatic reasons, complications recorded at predefined visits, or notified by investigators, will be compiled and reviewed annually. Actions will be taken if, halfway through the trial, clear imbalances regarding the safety of the participants become evident. Also, if evidence from other studies becomes available that definitely favors one or the other intervention and violates therapeutic uncertainty, DSMB members will decide if recruitment needs to be stopped (for further information, see [102]).

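### The safety comparison is written for the two intervention arms only, so as it stands it cannot estimate excess adverse events over TAU, and it conflicts with the stated three-group safety assessment

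*Protocol article*

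**What the plan says.** All references are to the protocol article; the statistical analysis plan is not available.

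- **Statistical methods, Additional analyses** (safety set): "The safety analysis will be based on the set of all randomized participants who were exposed to study intervention at least once".
- **Same sentence** (comparison): the analysis "includes calculation and comparison of frequencies and rates of adverse and serious adverse events reported in the two intervention groups".
- **Statistical methods, Primary outcome** (opening sentence): statistical methods are to assess "the homogeneity of the treatment groups, the efficacy endpoints, and the safety of the three treatment groups".
- **Abstract, Methods**: the design has "three arms (two add-on treatment groups [BLT, EI] and one treatment as usual [TAU] control group").
- **Participant timeline**: "Experimental groups will begin with the interventions the next day, while the control group continues with TAU which lasts for ten weeks".

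The section on analysis sets leaves the detailed allocation of participants to the full, per-protocol and safety sets to the statistical analysis plan.

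**The concern.** BLT and EI are add-ons, and usual care is allowed in every arm. The randomised contrast with TAU is therefore the one that isolates harm from the add-on.

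The side effects that the protocol anticipates are non-specific: nausea, headache and eyestrain with light, and minor injuries with exercise. The protocol itself likens the injury risk to that of ordinary daily life. Such events also occur in young people who receive neither intervention, so a count in the BLT or EI arm means little without the count under TAU. A BLT-EI comparison shows only how the two differ from each other.

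At stake is whether the planned analysis can support the article's statements that the interventions are essentially free of risk. A pilot trial meant to inform a phase-III decision should show the event rates of each add-on beside those of its control.

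**Working it through.** **1. Does the text leave TAU out?** The answer depends on what the article means by an intervention group, so both usages were tried.

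- *Strict usage.* The abstract counts BLT and EI as the two add-on groups and TAU as the control. The timeline has only the experimental groups starting an intervention. TAU participants then fail the exposure criterion and are also outside the two groups compared. Both halves of the safety sentence exclude them.
- *Loose usage.* The Primary outcome section describes the mixed model as "investigating the treatment effect with respect to all three intervention groups will be used", which counts TAU as an intervention group. TAU participants might then meet the exposure criterion, but the comparison still names two groups and not three.

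Under either usage the comparison covers two arms, while the opening sentence of the statistical section promises safety in three. The sections disagree, and no section states an adverse event comparison with TAU.

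**2. How many participants are affected?** The arm size comes from the sample size section: d = 0.5, two-sample t-test, two-sided alpha 0.10, power 80%, dropout about 30%, 219 in total, allocation 1:1:1.

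- t-test sample size: 51 per group.
- Dropout: 51 / (1 - 0.30) = 72.9, rounded up to 73 per arm.
- Total: 3 x 73 = 219, which matches the article.
- Power at two-sided 0.05 with 51 per group: 70.6%, against the stated 70%.

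The planning figures reproduce and are not in dispute. The safety comparison as written covers 2 x 73 = 146 of 219 participants and leaves out 73.

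**3. What can a BLT-EI comparison show?** Let the event risk be p under TAU, p + a under BLT and p + b under EI. The BLT-EI difference is (p + a) - (p + b) = a - b. It does not contain p, so it gives neither a nor b. If a = b, its expected value is 0 whatever the sample size.

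**4. What would adding TAU give?** The article gives no event rates, so these are assumptions. Take TAU 10%, BLT 20%, EI 20%, with 73 per arm.

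- BLT-EI: difference 0; half-width 1.96 x sqrt(2 x 0.20 x 0.80 / 73) = 1.96 x 0.0662 = 13.0 points.
- BLT-TAU (EI-TAU is the same): difference 10 points; SE = sqrt((0.20 x 0.80 + 0.10 x 0.90) / 73) = sqrt(0.25 / 73) = 0.0585; half-width 1.96 x 0.0585 = 11.5 points; 95% CI about -1.5 to 21.5.

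Other assumed rates for one add-on arm against TAU, 73 per arm, two-sided 0.05:

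| TAU | Add-on | Difference (points) | 95% half-width (points) | Power |
|---|---|---|---|---|
| 5% | 15% | 10 | 9.6 | 52% |
| 10% | 25% | 15 | 12.1 | 67% |
| 10% | 30% | 20 | 12.6 | 86% |
| 20% | 40% | 20 | 14.5 | 76% |

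Among these scenarios, only the 20-point excesses reach power of about 75% or more. Smaller ones can be described with an interval but not reliably detected.

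**The case against.** The strongest case on the other side has four parts.

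- *The sentence is not exhaustive.* It says what the analysis includes, the Primary outcome section already speaks of three groups, and the analysis plan could still bring TAU in. This limits the claim: it is not settled that TAU safety data will go unreported. It does not remove the conflict. The article does not leave the question open but states an exposure criterion and a two-group comparison. An analysis plan that follows them omits TAU, and one that adds TAU departs from them.
- *The trial still has the data.* A reader might infer that the trial itself cannot detect harm over usual care. The article does not support that. Nothing says that adverse events under TAU go uncollected, and control participants attend the same assessments. The limitation lies in the analysis as described.
- *Monitoring may cover it.* A reader might also infer that the monitoring board lacks TAU data, or that adverse events are asked about differently by arm. Neither is shown. The Monitoring section says only "Actions will be taken if, halfway through the trial, clear imbalances regarding the safety of the participants become evident" and does not name the arms. Nor does the article describe arm-specific questioning.
- *The gain is small.* This is a pilot, few adverse events are expected, and the 20% against 10% illustration has an interval that includes zero. This stands, and it lowers the severity.

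TAU should also not be read as no treatment. It is active usual care, including medication and psychotherapy, and is permitted in all arms. The comparison with it measures the harm of adding BLT or EI to that care.

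**Conclusion.** The point holds as a flaw in the written safety analysis. The article contradicts itself on whether safety is compared in two groups or three, and the more specific sentence leaves out the control arm, 73 of 219 participants. Followed literally, it cannot estimate excess adverse events of either add-on over TAU, and an excess common to both would have an expected difference of zero.

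The algebra behind this needs no assumption about event rates. The illustrated intervals and power values rest on assumed rates and on 73 evaluable participants per arm, so dropout would widen them.

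Severity is moderate. The primary estimate, the type I error and the sample size are untouched, and at this size a comparison with TAU is mainly descriptive. It should be corrected before the analysis so that the safety comparison is not chosen after the data are seen.

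**What to change.** Reconcile the Additional analyses and Primary outcome sections, and carry the same definition into the statistical analysis plan:

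1. Define the safety set as all randomised participants, including TAU, analysed by the condition received (BLT, EI or TAU). Say where a participant allocated to BLT or EI who never starts is counted.
2. Replace the two-group comparison with adverse and serious adverse event frequencies and rates for all three arms, giving BLT-TAU and EI-TAU differences with 95% confidence intervals. The BLT-EI comparison can stay as an addition.
3. Present these results as descriptive, and use an interval method suited to small counts.

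The cost is one sentence in the text and one column in the safety tables. The TAU arm is already randomised and already assessed at the same visits, so no further participants or visits are needed.

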#### Definition of analysis sets

Each participant’s allocation to the different analysis populations (full analysis set according to the ITT principle, PP analysis set, safety analysis set) will be defined and in detail explained in the statistical analysis plan which is finalized before the analysis. During the data review, deviations from the protocol will be assessed as “minor” or “major.” Major deviations from the protocol will lead to the exclusion of a participant from the PP analysis set.

### Monitoring

The study will be monitored by the KKS Heidelberg, a university-based institution which is independent from other trial staff and very experienced in monitoring clinical trials. Monitoring will be done by on-site and off-site visits and frequent communication (letters, telephone, facsimile, email) by a clinical monitor according to SOPs of the KKS and the study-specific monitoring manual. The monitor will ensure that the trial is conducted according to the protocol and regulatory requirements by review of source documents, entries into the CRFs, and essential documents. The monitor will document the visits in a report for the PI as well as the local primary investigator. The site will be provided with a follow-up letter of the findings and the necessary actions to be taken. As the monitoring strategy will consider current aspects of risk-based quality management, frequency of monitoring activities per site will vary depending on recruitment, experience, and general performance, e.g. quality of documentation of the individual trial sites. If there are major findings during monitoring or an audit, the investigational site might be closed by the trial coordinator/PI.

In addition to the standardized monitoring procedures, an independent DSMB has been established that supervises the conduct of the trial and issues recommendations for early termination, modifications, or continuation of the trial, if necessary. The DSMB involves two independent clinical experts and one biometrician for monitoring the progress of the trial and ensure adherence to protocol. The role of the DSMB will be to monitor the progress of the trial and to ensure adherence to protocol. The character of the interventions under investigation makes unexpected SAEs extremely unlikely. For pragmatic reasons, complications recorded at predefined visits, or notified by investigators, will be compiled and reviewed annually. Actions will be taken if, halfway through the trial, clear imbalances regarding the safety of the participants become evident. Also, if evidence from other studies becomes available that definitely favors one or the other intervention and violates therapeutic uncertainty, DSMB members will decide if recruitment needs to be stopped (for further information, see [102]).

### Ethics and dissemination

Before the first individual has been enrolled onto the trial, all ethical and legal requirements were met. Study protocol, participant information, and the respective consent form were approved by the responsible ethical committees before start of the trial. The study protocol was first ethically reviewed and approved by the institutional review board (IRB) of the Medical Faculty, Goethe University, Frankfurt am Main, German (No. 353/16, 13 January 2017). Subsequent approval of this vote was done by the ethical committee of Vall d’Hebron Research Institute, Barcelona, Spain (No. PR(AG)105/2017, 19 April 2017), King’s College London, UK (No. 17/LO/0958, 11 July 2017), and Radboud University Medical Centre, Nijmegen, The Netherlands (No. 2017-3238, 5 October 2017). Any modifications to the protocol which may impact on the conduct of the study, potential benefit of the participant, or may affect participant safety, including changes of study objectives, study design, participant population, sample sizes, study procedures, or significant administrative aspects, will require a formal amendment to the protocol. The IRB of the PI, as well as the IRB of the participating centers and trial registries will be informed of all subsequent protocol amendments which require approval in accordance with local legal requirements.

The procedures set out in this trial protocol, pertaining to the conduct, evaluation, and documentation of this trial, are designed to ensure that all persons involved in the trial abide by GCP (as far as applicable) and the ethical principles described in the current revision of the Declaration of Helsinki. The trial is carried out in keeping with local legal and regulatory requirements, although German Drug Law and Medical Device Law are not applicable. Each site’s PI ensures that all persons assisting with the trial are adequately informed about the protocol, any amendments to the protocol, the trial treatments, their trial-related duties, and functions. The particular local investigator maintains a list of sub-investigators and other appropriately qualified persons to whom he or she has delegated significant trial-related duties. Equally, each local primary investigator ensures that the respective center is responsible for the correct application of the therapy-manuals.

Before being enrolled in the clinical trial, the adolescent’s caretaker(s) and the adolescent participant as well as the young adult participant must consent to the participation of the participant after the nature, scope, and possible consequences of the clinical trial have been explained to them in an understandable oral and written form. Participants as well as their caretakers can withdraw from the study any time without giving a reason. Informed consent will be obtained by the local investigator and stored in the ISF at each study site. A copy of the signed informed consent document will be given to the adolescent’s caretaker(s) and the young adult participant. The documents will be in a language understandable to the individual and his/her caretakers and specify who informed him or her. For this reason, there are three information documents in the presented study: one for participating adolescents; one for the parents/caretakers of the participating adolescents; and one for young adults.

Throughout the trial, participants are pseudonymized. Trial data stored on a computer will be stored in accordance with the local data protection law and will be handled in strictest confidence. Distribution of these data to unauthorized persons is strictly prohibited. The appropriate regulations of local data legislation will be fulfilled in their entirety. Authorized persons (e.g. clinical monitors, auditors) regularly inspect the participant-related data collected during the trial ensuring the data protection law (see monitoring). The local primary investigator of each study site will maintain a personal participant identification list (participant numbers with the corresponding names) to enable records to be identified.

The trial statistician as well as the PI, and, in case of SAEs, members of the DMSB, have access to the final trial set for statistical analyses. After the publication of the primary and secondary outcome measures, all responsible investigators at all study sites will get access to the data to be able to reanalyze the data with regard to specific additional research questions. In case of an external request for replication, the respective statistical analysis will be provided by the trial statistician.

Trial results will be reported to participants, healthcare professionals, the public, patient advocacy groups, and other relevant groups via publications, conferences, press releases, and public talks. Authorship eligibility guidelines according to the International Committee of Medical Journal Editors [103] will be adhered to. No professional writers will be involved in any publication.

